### Economic evaluation

We will determine if the intervention is cost-effective, by comparing utilities derived from EQ-5D and DEMQOL-U, with costs. Costs will be separately determined from health service, public-sector multi-agency and private or informal care perspectives. We will consider time frames of the trial period, and the anticipated remaining lifespan of participants, using Markov modelling. We will also use a social return on investment model [58]. These analyses will be subject to a separate protocol.

### Adverse events

Adverse event (AE) monitoring will begin when a participant has been randomised and will continue for 15 months. We will record AEs which are defined as serious (involving death, life-threatening events, hospitalisation, significant disability or incapacity) or which are potentially related to the intervention or to exercise undertaken independently. Inter-current illness, progression of dementia, loss of function, hospitalisation and death are likely to be common in this population given their age and frailty. We will assess all reported AEs for severity and relatedness to the intervention.

The intervention group will have more contact with professional staff than the control group, and therefore greater opportunity to report AEs, presenting a potential bias. We will screen falls diaries and medical records to ascertain core AEs across both arms. For purposes of comparing the safety of the intervention, we will consider ’deaths’, ’hospital admissions’ and ’falls’ to be core AEs. These will be ascertained and analysed as part of the core research dataset, independently of incidental reporting, and should therefore be more robust to information bias.

### Data management

A data management plan will be drawn up by NWORTH CTU as part of the trial setup. Data will be entered locally using the MACRO data entry system. For each time point and for each site, 5% of the cases entered into MACRO will be checked against the data recorded on the paper case report forms. All study co-applicants and researchers will have access to the final trial dataset. There are no contractual agreements limiting access for investigators.

### Statistics and data analysis

A Statistical Analysis Plan will be agreed between a CTU trial statistician, a second statistical advisor (based at the CTU) and the Chief Investigator, before completion of data collection. The Data Monitoring and Ethics Committee (DMEC) and the Programme Steering Committee (PSC) will approve the Statistical Analysis Plan.

Analyses will be undertaken by the CTU and will be performed blind to group allocation.

The first 50 randomised participants will constitute the sample for an internal pilot, to check on recruitment and data completion. There will be no other interim analyses.

### Sample size and justification

The primary outcome is the Disability Assessment for Dementia (DAD) at 12 months [37]. A sample size of 184 participants per group, including 23% attrition (based on previous studies [10, 31]), has 80% power to detect changes in the disability outcome, DAD, with effect size 0.5 (11 points on a baseline of 70, standard deviation 22, data from [10, 13]). This sample size has been rechecked using data from the feasibility study and confirmed to be a conservative estimate.

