### Study design

A multi-centre, individually randomised, pragmatic, parallel-group, controlled trial will be conducted (Fig. 1). Participants will give informed consent, and will be randomised to one of two arms: the intervention arm comprising supervised therapy, or the control arm, comprising falls risk assessment and advice (Fig. 2). Mixed methods will be used to undertake process evaluation [35] and economic analyses. The Standard Protocol Items: Recommendations for Interventional Trials (SPIRIT) checklist is provided as Additional file 1.

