### Recruitment

The trial will recruit 368 participants and family or carer dyads from different sites in England. Recruitment will be carried out by a study researcher, who will assess mental capacity, take consent and collect baseline data from both members of the dyad.

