### Assessment of efficacy

Analyses will be conducted on an intention-to-treat basis. Missing data for outcome measures will be imputed, using multiple imputation, if more than 5% of the data are missing and data are shown to be missing at random.

We will compare the DAD scores between the intervention and the control groups, adjusting for stratifying variables and any baseline imbalances in an ANCOVA model. Adjusted mean differences between groups and standardised effect size estimates (equivalent to Cohen’s *d* [59]) will be calculated.

Rate of falls will be compared between the intervention and the control groups using the incidence rate ratio, from a negative binomial regression model, adjusted for baseline imbalance or variables with prognostic importance [60, 61].

Other secondary outcomes will be compared between the intervention and the control groups using ANCOVA to adjust for baseline imbalance or variables with prognostic importance.

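### The sample size figures do not fit together: 184 per group with 23% attrition gives about 98.7% power for effect size 0.5, and 80% power only at about 0.33 (7.3 DAD points)

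*Protocol article*

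**What the plan says.** The section Sample size and justification of the protocol article names DAD at 12 months as the primary outcome and gives the calculation in one sentence. The planned number is "A sample size of 184 participants per group, including 23% attrition". This is said to have "80% power to detect changes in the disability outcome, DAD, with effect size 0.5 (11 points on a baseline of 70". The effect size is explained as "effect size 0.5 (11 points on a baseline of 70, standard deviation 22, data from [10, 13". A further sentence says that the number was rechecked against feasibility data and found to be conservative.

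Three other places bear on the point:

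- Recruitment confirms the total: "The trial will recruit 368 participants and family or carer dyads from different sites in England". Since 2 × 184 = 368, the 184 is a per-arm figure.
- Study design describes the trial as follows: "A multi-centre, individually randomised, pragmatic, parallel-group, controlled trial will be conducted".
- Assessment of efficacy compares DAD scores "adjusting for stratifying variables and any baseline imbalances in an ANCOVA model". It mentions no clustering term.

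The article states no significance level, no design effect and no multiplicity allowance for the sample size.

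**The concern.** The effect size agrees with its own components, since 11/22 = 0.5. But 0.5 is a fairly large standardised difference, and a two-arm comparison at 80% power usually needs only a little over 60 analysed per arm to detect it. A plan for 184 per arm is far above that, and 23% attrition does not close the gap.

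The target difference is the benchmark for reading the primary result. If the article says the trial was sized for 11 points when the number really corresponds to about 7, two misreadings are open. A significant result could be taken as support for an 11-point benefit although a much smaller observed difference would reach significance. A null result could be taken to exclude only large effects, when the trial would be informative about considerably smaller ones. The same sentence is also the published justification for enrolling 368 people with cognitive impairment, each with an informant.

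**Working it through.** **Inputs.** From Sample size and justification: 184 randomised per group, 23% attrition, 80% power, difference 11, SD 22, d = 0.5. From Recruitment: 368 in total. Assumed: two-sided α = 0.05 and a two-sample comparison of means. Results use the noncentral t distribution unless marked as a normal approximation.

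**1. Try to reproduce the plan's number from its own inputs.**

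Normal approximation: n = 2(z₀.₉₇₅ + z₀.₈₀)²/d² = 2(1.960 + 0.842)²/0.25 = 62.8, so 63 per group. The t distribution gives 64.

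Allowing for attrition: 64/(1 − 0.23) = 83.1, so 84 per group and 168 in total. The plan has 184 and 368, and 368/168 = 2.2. The figure is not reproduced.

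**2. Power of the planned number.**

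Analysed per group: 184 × 0.77 = 141.7, about 142.

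Noncentrality: d√(n/2) = 0.5 × √71 = 4.21. Normal approximation: Φ(4.21 − 1.96) = 98.8%. With the t distribution the power is 98.7%, against the stated 80%.

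**3. Effect size that matches the planned number at 80% power.**

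Normal approximation: (1.960 + 0.842) × √(2/142) = 0.332. With the t distribution it is 0.334, and 0.334 × 22 = 7.3 points. Working back, 142/0.77 = 184.4, which is very close to the planned 184.

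If the 11 points are kept, the matching SD is 11/0.3336 = 33.0.

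**4. Smallest significant observed difference (no baseline adjustment).**

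SE = 22 × √(2/142) = 2.61, and 1.96 × 2.61 = 5.1 points (0.23 SD).

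**5. Could another reading rescue the 80%?**

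| Reading | Result |
|---|---|
| 184 is the total (71 analysed per arm) | Power about 84%; excluded by the per-group wording and by 368 |
| Attrition applied as n × 1.23 (184/1.23 = 149.6 analysed) | Power 99.1% |
| No attrition (184 analysed) | Power 99.8% |
| One-sided 5% | 80% power at d of about 0.30, so a wider gap |
| Two-sided 1% | Power 94.7% |
| Two-sided 0.1% | Power 81% |
| Two-sided level giving exactly 80% | About 0.0009; nothing in the article suggests it |
| Bonferroni for 10 or 20 tests | 139 or 156 randomised per group |
| 90% or 95% power instead of 80% | 111 or 136 randomised per group |
| Unadjusted change score, zero correlation with baseline | 164 randomised per group |
| Design effect | About 2.2 needed (142/64); none is stated, and randomisation is individual |

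The randomised numbers in the table use the normal approximation.

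**6. Effect of baseline adjustment.** ANCOVA multiplies the SD by √(1 − r²). For an assumed baseline correlation r of 0.3 to 0.7, power at 11 points is at least 99.3%, and the difference detectable with 80% power falls to between 7.0 and 5.2 points. Adjustment widens the gap.

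**The case against.** The best case on the other side does not defend the sentence. It argues about which figure is at fault and how much it matters.

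- **The article does not show which input is wrong.** This stands. Effect size, SD or power could be mis-stated, and a condensed article cannot exclude an inflation factor recorded only in the full protocol. But such a factor would have to be about 2.2, and nothing in an individually randomised design analysed by ANCOVA points to one. If one was used, the printed sentence is still wrong as it reads.
- **The number is described as conservative.** This tells readers that the feasibility data did not call for more participants. It does not make the 80% figure true, and it does not disclose a more than two-fold excess over the stated inputs.
- **Part of the gap between 5.1 and 11 points is ordinary.** Correct. In any trial with exactly 80% power the significance threshold is about 1.96/2.80 = 0.70 of the target, so a trial properly sized for 11 points would reach significance at about 7.7. The part due to the misstatement is about 7.7 − 5.1 = 2.6 points.
- **The estimate, test and confidence interval are unaffected.** Also correct. The damage is to the benchmark against which they are read, and to the stated basis for recruiting 368.
- **A difference of 7.3 points is solved back from the sample size, not chosen for clinical reasons.** This stands, and is why the correction must also say which difference counts as important.

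**Conclusion.** The point holds. At two-sided 5%, 184 per group with 23% attrition, 80% power, and an effect size of 0.5 cannot all be true. The planned number gives about 98.7% power for 11 points at SD 22, and 80% power at about 0.334 SD (7.3 points). The stated inputs justify 168 participants, not 368.

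The only outside assumption is the significance level. The conclusion survives at two-sided 1%, and the gap grows at one-sided 5%; only a level near 0.0009 would remove it. The direction is safe for power: if SD 22 is right, the trial is more than adequate for 11 points. If the intended SD was near 33, the published SD and effect size are wrong and the precision figures above change with them. Only the sponsor can say which applies.

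**What to change.** Keep 368 and correct the sentence. If SD 22 is right, it could read:

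*With 184 randomised per group and 23% attrition (142 analysed per group), the trial has 80% power at a two-sided 5% level to detect a standardised difference of 0.33 (7.3 DAD points, SD 22), and about 99% power for 0.5 (11 points).*

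If 11 points was meant with an SD near 33, correct the SD and the effect size instead (11/33 = 0.33). If an inflation factor was applied, give its value and its reason.

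In every case state the significance level and its sidedness, and name the difference that will serve as the benchmark for clinical importance when the confidence interval is read. The last choice needs its own justification, because a detectable difference derived from the sample size does not provide one.

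The cost is one sentence in the protocol and the same sentence in the SAP, which the article says will be agreed before data collection ends. Recruitment and the planned analysis do not change.

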### Baseline comparison

Baseline variables will be compared across groups using means, medians or proportions as appropriate.

### Assessment of efficacy

Analyses will be conducted on an intention-to-treat basis. Missing data for outcome measures will be imputed, using multiple imputation, if more than 5% of the data are missing and data are shown to be missing at random.

We will compare the DAD scores between the intervention and the control groups, adjusting for stratifying variables and any baseline imbalances in an ANCOVA model. Adjusted mean differences between groups and standardised effect size estimates (equivalent to Cohen’s *d* [59]) will be calculated.

Rate of falls will be compared between the intervention and the control groups using the incidence rate ratio, from a negative binomial regression model, adjusted for baseline imbalance or variables with prognostic importance [60, 61].

Other secondary outcomes will be compared between the intervention and the control groups using ANCOVA to adjust for baseline imbalance or variables with prognostic importance.

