### Follow-up and outcomes

Each participant will take part for 15 months. After 6 months, informants will be asked to complete the EQ-5D-5L proxy [39], DEMQOL-U items from the DEMQOL measure [41] and the Short CSRI [51] about the participant, via post, with telephone calls to prompt or support as needed. The main follow-up is after 12 months (+/− 4 weeks), when two researchers will visit the dyads at home to collect outcome data by interviewing the participant and informant separately (Table 1). In the feasibility study, the follow-up rate at 12 months was 80% without differential loss between arms (Goldberg et al., Promoting Activity, Independence and Stability in Early Dementia (PrAISED): a feasbility, multisite, randomised controlled trial, forthcoming).

Participants will keep a monthly diary for falls and service use between months 0 and 15, with telephone calls to prompt or support as needed. Therapists delivering the intervention sessions will not be permitted to use or prompt the use of the monthly diary for either study arm.

For falls, the incidence rate ratio will be compared for the intervention and control groups. For all other outcome measures, the standardised effect size estimate (*d*) of the difference between the groups’ follow-up scores will be based on analysis of covariance (ANCOVA), which will take into account the baseline scores on the measures. Data will be aggregated using mean score unless descriptive statistics show the data to be substantially skewed or non-normal.

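### The primary DAD ANCOVA admits covariates by observed baseline imbalance, not by prognostic value, and the section that defines it does not name baseline DAD

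*Protocol article*

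**What the plan says.** Two sections of the Protocol article describe the ANCOVA.

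- **Assessment of efficacy** defines the primary comparison of DAD scores as "adjusting for stratifying variables and any baseline imbalances in an ANCOVA model". It does not mention baseline DAD. The stratifiers, listed under Randomisation, are site, co-resident carer and falls history.
- **Follow-up and outcomes** says that, for every outcome except falls, the standardised group difference "will be based on analysis of covariance (ANCOVA), which will take into account the baseline scores on the measures". No condition is attached.

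Assessment of efficacy also allows the falls and other secondary analyses to adjust for prognostic variables as well as for imbalance. The primary sentence has no reference to prognosis; beyond the stratifiers, imbalance is its only criterion.

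**The concern.** A covariate earns its place in an ANCOVA because it predicts the outcome. A strong predictor should be in the model even when the arms are perfectly balanced on it, and a chance imbalance in a variable unrelated to outcome is no reason to adjust. The stated rule works the other way round. The Baseline data collection section lists 13 domains, many with several scales, so some chance imbalance is to be expected, and the primary model would then depend on where it fell.

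The variable most likely to matter is baseline DAD. If Assessment of efficacy were applied on its own, baseline DAD would enter only when imbalanced. In most trials it would then be left out, precision would be given up, and the reported standard error would not match the true variability of the estimate.

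**Working it through.** **Inputs from the article (Sample size and justification).** Endpoint: "The primary outcome is the Disability Assessment for Dementia (DAD) at 12 months". Size: "A sample size of 184 participants per group, including 23% attrition". Effect: "with effect size 0.5 (11 points on a baseline of 70, standard deviation 22". Power: 80%.

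**Assumptions.** The article gives no alpha, so two-sided 5% is used. It gives no correlation r between baseline and 12-month DAD; 0.5 and 0.7 are the main cases, with 0.3 and 0.8 as outer values. It gives no imbalance criterion (a detail that may properly sit in the SAP), so three triggers are tried: p < 0.05, and absolute standardised difference (SMD) above 0.2 or above 0.1.

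**Step 1: the plan's own figure.** n per arm = 2 × (1.960 + 0.842)² / 0.5² = 62.8, so 63. Allowing for attrition, 63 / 0.77 = 81.8, so 82, against 184 stated. The stated size is not reproduced. In reverse, 184 × 0.77 = 141.68 analysable per arm, which gives 98.8% power at 0.5 SD. The effect detectable with 80% power is 2.802 × √(2/141.68) = 0.333 SD, or about 7.3 points. That mismatch is a separate matter; it matters here only because it makes both 0.5 and 0.333 SD relevant effects.

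**Step 2: value of baseline DAD when always included.** SE = 22 × √(1 − r²) × √(2/141.68).

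- Omitted: 22 × 0.1188 = 2.61 points.
- r = 0.5: 2.61 × 0.866 = 2.26 points, 13% smaller.
- r = 0.7: 2.61 × 0.714 = 1.87 points, 29% smaller.

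**Step 3: baseline DAD included only if imbalanced.** Simulation: 40,000 trials per setting, 141 per arm, bivariate normal, SD 22, no other covariates. Model SE is the root mean square of the reported SE; true SD is the observed spread of the estimate.

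| r | Rule | Trials adjusted | Type I error | Model SE / true SD | Power at 0.333 SD (loss) | Power at 0.5 SD (loss) |
|---|---|---|---|---|---|---|
| 0.5 | always | 100% | 4.8% | 2.27 / 2.25 | 89.7% | 99.8% |
| 0.5 | p < 0.05 | 4.9% | 4.2% | 2.60 / 2.51 | 80.7% (8.9) | 99.0% (0.8) |
| 0.5 | SMD > 0.2 | 9.2% | 3.9% | 2.59 / 2.46 | 81.4% (8.2) | 99.2% (0.6) |
| 0.5 | SMD > 0.1 | 40.2% | 3.6% | 2.49 / 2.30 | 85.1% (4.5) | 99.6% (0.3) |
| 0.7 | always | 100% | 4.8% | 1.87 / 1.86 | 97.5% | 99.99% |
| 0.7 | p < 0.05 | 4.9% | 3.5% | 2.59 / 2.42 | 81.7% (15.9) | 99.2% (0.8) |
| 0.7 | SMD > 0.2 | 9.2% | 3.0% | 2.56 / 2.32 | 83.0% (14.5) | 99.4% (0.6) |
| 0.7 | SMD > 0.1 | 40.2% | 2.7% | 2.35 / 1.97 | 90.3% (7.3) | 99.9% (0.1) |

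Losses are percentage points against always adjusting, taken from unrounded rates. At 0.333 SD the loss is 1.8 to 3.3 points for r = 0.3 and 7.0 to 17.6 points for r = 0.8. Never adjusting gives about 79.7% power at 0.333 SD and 98.7% at 0.5 SD, so no version of the imbalance rule falls below the unadjusted analysis.

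**Step 4: why the error is on the conservative side.** In the trials where baseline DAD is left out, the arms are close on it, so the estimate varies less than an unadjusted estimate would. The reported SE still carries the full unadjusted residual variance, so it is too large.

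**The case against.** The strongest reply is that baseline DAD is already in the model. Follow-up and outcomes includes baseline scores without condition, and its wording covers the primary outcome. Assessment of efficacy is silent on baseline DAD; it does not exclude it. The sections can be read as additive, one supplying the baseline score and the other the further covariates. This stands. A reader might infer a flat contradiction, or that the plan has decided to drop baseline DAD when it is balanced; the text supports neither. The figures in the table therefore apply only if Assessment of efficacy is followed alone. The effect of adding other imbalanced covariates to a model that already holds baseline DAD was not quantified.

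It is also fair to say that imbalance is judged on baseline data and not on outcomes, that the analysis is to be blind to allocation, and that an SAP is to be agreed before data collection ends. These limit any steering of the result towards one arm, and the exact covariate list may be settled there. They do not answer the point in full: blinding does not stop the covariate list depending on observed arm differences, and an SAP that faithfully follows Assessment of efficacy inherits the rule.

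Finally, at the planned 0.5 SD the power loss is negligible. That is correct, and the larger losses depend on a smaller true effect and on an assumed correlation.

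**Conclusion.** The point holds as a stated, inferior rule for choosing covariates in the primary model, combined with an omission that leaves the role of baseline DAD to be inferred from another section.

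Its size is conditional. If Follow-up and outcomes governs, there is no loss through baseline DAD, and what remains is the open-ended imbalance rule. If Assessment of efficacy is applied alone, with r between 0.5 and 0.7 and about 142 per arm, type I error is about 3% to 4%. Power lost against always adjusting is then under 1 point at 0.5 SD and roughly 5 to 16 points near 0.33 SD, depending on the trigger.

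Two stronger conclusions are tempting and are not supported. False positives are not inflated; the test errs on the conservative side. Nor does the rule take power below an unadjusted two-group analysis; what is given up is additional precision. Alpha, the correlation and the triggers are all assumptions.

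**What to change.** In Assessment of efficacy, state the primary model as 12-month DAD on arm, baseline DAD, site, co-resident carer and history of falls, in agreement with Follow-up and outcomes. Delete the reference to baseline imbalances from the primary model. Name any further covariate in advance, for its prognostic value and before outcome data are seen. Keep adjustment for variables found to be imbalanced only as a labelled sensitivity analysis, and carry the same model into the SAP.

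The cost is a change of wording. Baseline DAD is already part of the baseline assessment, so no new data are needed.
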